### Randomization sequence generation and allocation concealment

Pre-existing maps of HFCAs were used to classify households as belonging to a specific HFCA, which serve as the unit of randomization. To ensure balance across large and small HFCAs, which could potentially affect the quality of program implementation and other related unobserved confounding factors, HFCAs were characterized as having either a large or small population catchment size. This classification was based on a cut-point obtained from the mean population catchment size across the 60 HFCAs. Within the high and low transmission strata and the large and small population catchment size classifications, the random allocation rule will be used to assign HFCAs to the fMDA-DHAp, MDA-DHAp, or control group. As a result of this process and the stratification outlined above, the 60 total HFCAs are split into 10 HFCAs per treatment group (MDA, fMDA, and control) in the high transmission strata (n = 30 HFCAs), and 10 HFCAs per treatment group (MDA, fMDA, and control) in the low transmission strata (n = 30 HFCAs).

After allocation, the appropriate intervention will be implemented in the entire catchment area according to treatment group assignment. Allocation of study arms will not be blinded to the deliverers of the intervention or to the main investigators, as delivery of the intervention precludes the possibility of allocation concealment. However, data collectors in the follow-up parasite prevalence survey, as outlined below, will be blinded to allocation. All primary analyses will also be blinded to analysts by the use of concealed code for the study arm variables in the final dataset.

### Primary outcome measures

Primary outcomes used to measures the impact of the MDA-DHAp and fMDA-DHAp interventions, as compared to a control of standard of care, are:Parasite prevalence during the high transmission season among children < six-years-old: defined as the proportion of children < six-years-old (≥three months to < six-years-old) with *P. falciparum* infection (based on both RDT and PCR) out of all children < six-years-old tested within the 2014 and 2015 cross-sectional parasite surveys.*P. falciparum* infection incidence rate among individuals ≥ three-months-old*:* defined as the number of individuals ≥ three-months-old with a new *P. falciparum* infection (based on PCR) divided by the total person-time observed among a cohort of individuals ≥ three-months-old followed up on for a 12-month-period.Total and confirmed outpatient (OPD) malaria case incidence and inpatient (IPD) malaria case incidence among all ages: defined as the number of OPD and IPD malaria confirmed and suspected cases per person per year, as ascertained from the routine rapid reporting system; facility catchment population size estimates will be used for the exposure denominator.RDT positivity: defined as the proportion of all individuals tested by RDT at each round of the fMDA and MDA interventions (and among a contemporaneous sample in the control group), with a positive RDT, among the population of individuals ≥ three-months-old.

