**Methods/design:**

The study will be conducted along Lake Kariba in Southern Province, Zambia; an area of low to moderate malaria transmission and high coverage of vector control. A community randomized controlled trial (CRCT) of 60 health facility catchment areas (HFCAs) will be used to evaluate the impact of two rounds of MDA and fMDA interventions, relative to a control of no mass treatment, stratified by high and low transmission. Community residents in MDA HFCAs will be treated with DHAp at the end of the dry season (round one: November to December 2014) and the beginning of the rainy season (round two: February to March 2015). Community residents in fMDA HFCAs will be tested during the same two rounds for malaria parasites with a rapid diagnostic test; all positive individuals and all individuals living in their household will be treated with DHAp. Primary outcomes include malaria parasite prevalence (n = 5,640 children aged one month to under five-years-old), as measured by pre- and post-surveys, and malaria parasite infection incidence (n = 2,250 person-years among individuals aged three months and older), as measured by a monthly longitudinal cohort. The study is powered to detect approximately a 50 % relative reduction in these outcomes between each intervention group versus the control.

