The results from the previous MTAT trials also suggest that alternatives to the MTAT antimalarial delivery strategy are needed. One alternative strategy to avoid some important limitations of MTAT involves treating all individuals within a specified target area with an effective antimalarial, irrespective of having a parasite infection identified by an RDT, which would constitute community-wide mass drug administration (MDA) [9]. There are several potential advantages of using MDA, especially if coupled with DHAp (MDA-DHAp), over MTAT-AL. First, RDTs used for diagnosis in the previous MTAT strategy have been shown to miss up to 50 % of low-density malaria parasite infections [10], and thereby leave a substantial reservoir of infection in the community untreated, which may then sustain continued transmission. Such individuals with low-density parasite infections missed by RDTs under the MTAT will receive treatment under MDA. Second, because MDA-DHAp may also provide effective chemoprophylaxis against new infections for the entire target population (irrespective of RDT result), it is expected to provide a larger chemoprophylactic and chemo-suppressive effect to the community than limiting drug administration to only those individuals testing positive for a malaria infection by RDT [10, 11]. As a result, MDA-DHAp is potentially more effective and cost-effective than MTAT, due both to clearance of low-density infections and by prevention of new infections in the entire population [12].

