**Fig. 4 Fig4:**
[figure not shown]
Flow chart for cohort enrollment and follow-up visit for both high and low transmission strata. *AL*: Artemether-lumefantrine; *DHAp*: Dihydroartemisinin plus piperaquine; *MDA*: Mass drug administration; *fMDA*: focal mass drug administration; *RDT*: Rapid diagnostic test; *DBL*: Dried blood spots

Capillary blood from a finger prick from all enrolled participants will be collected at the time of enrollment for detection of a malaria parasite infection by RDT, microscopy, and PCR. For individuals enrolled into the cohort from the round one of MDA HFCAs, all will be offered an appropriate dose of DHAp the same as those in the MDA study, irrespective of RDT result. For individuals enrolled into the cohort from the round one fMDA HFCAs, those testing positive by RDT or in households with any member testing positive by RDT will be offered an appropriate dose of DHAp the same as those in the fMDA study. Individuals enrolled into the cohort in control HFCAs testing positive by RDT will receive age and weight appropriate formulations of AL, as per standard of care guidelines [14].

Enrolled individuals within the MDA, fMDA, and control HFCAs will then be followed up on every four weeks from enrollment date for collection of blood for an RDT, microscopy, and DBS for PCR, until the study’s conclusion in November 2015. Any individual testing positive for circulating malaria antigen by RDT during any visit after enrollment will receive treatment of age- and weight-appropriate doses of AL, as per standard of care guidelines [14].

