#### Longitudinal cohort

##### High transmission strata

The CV for infection incidence was based on estimates of OPD confirmed case incidence for HFCAs for 2012 (CV = 0.50). Based on the 30 HFCAs available in the high transmission strata, a statistical power of 80 %, a probability of committing a type two error of 5 % (one-tailed test), a sample size of 25 individuals aged three-months-old and older per HFCA (cluster) per treatment group will be needed to detect an absolute detectable difference in 12-month cumulative parasite infection incidence between any two groups from an assumed baseline of 1.8 infections per person per year to 0.91 infections per person per year (a 49 % relative reduction). With a loss to follow-up rate assumed to be 33 %, a sample size of 375 individuals per treatment group (38 per HFCA) will be enrolled and followed up on monthly, totaling 1,125 individuals aged three-months-old and older enrolled in the cohort study in the high transmission strata (Additional file 1: Table S3).

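### Outcome two is defined as people infected over total person-time, but it is powered on, and modelled for, recurrent infections per person-year

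*Protocol article*

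**What the plan says.** **Definition.** Under Primary outcome measures, outcome two is "defined as the number of individuals" above the age limit who acquire a new infection. The sentence then describes it as an "infection (based on PCR) divided by the total person-time observed among a cohort of individuals", observed for 12 months. The numerator is persons and the denominator is all observed time.

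**Sample size.** Under Longitudinal cohort, high transmission strata, the target runs "from an assumed baseline of 1.8 infections per person per year to 0.91 infections per person per year", a fall put at 49%. The article names the quantity being compared an "absolute detectable difference in 12-month cumulative parasite infection incidence between any two groups". The low-stratum paragraph uses 0.6 to 0.28 infections per person per year, called 53%. The abstract sums the cohort to "2,250 person-years among individuals aged three months and older".

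**Analysis.** The Statistical analysis plan section names a Poisson or negative binomial model for infection incidence and allows for repeated measures within individuals.

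**Sampling and treatment in the cohort.** Blood for PCR is taken at enrolment and every four weeks, but treatment decisions do not use PCR. The Longitudinal cohort section says: "For individuals enrolled into the cohort from the round one of MDA HFCAs, all will be offered an appropriate dose of DHAp". In fMDA areas the offer goes to RDT-positive people and members of their households. In control areas only RDT-positive people are treated. After enrolment, a positive RDT triggers treatment in every arm. The Background says that RDTs "have been shown to miss up to 50 % of low-density malaria parasite infections".

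**The concern.** A person count over total person-time and an infection count over person-time are two different effect measures. They agree only when infection is rare, and 1.8 per person-year is not rare. If the outcome is programmed as defined, the trial reports a compressed effect, most strongly in the high stratum, and reports something other than what its sample size was built for.

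The same sentence raises a second, softer issue. The outcome depends on the infection being *new*, yet infections that PCR detects and the RDT misses are left untreated in control areas, and in fMDA households without a positive RDT, while everyone in MDA areas is offered treatment. Unless *new* is given one fixed meaning, an infection already present at enrolment could be counted as incident more often in control than in MDA. That would favour MDA.

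**Working it through.** **Inputs (all from the protocol article).** 10 HFCAs per arm per stratum; 25 (high) and 27 (low) people per HFCA; CV 0.50; power 80%; one-sided 5%, which the article prints as a type two error and which is used here as the type I error; 375 enrolled per arm per stratum; 33% loss to follow-up.

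**1. Reproduce the stated design.** Unmatched cluster formula for rates, with one person-year per individual:

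c = 1 + (z_α + z_β)² × [(λ0 + λ1)/y + k²(λ0² + λ1²)] / (λ0 − λ1)², where (1.645 + 0.842)² ≈ 6.18.

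- High: [2.71/25 + 0.25 × (3.24 + 0.8281)] / 0.89² = 1.1254/0.7921 = 1.421, so c = 1 + 6.18 × 1.421 = 9.78. Power with 10 clusters is 80.8%.
- Low: [0.88/27 + 0.25 × (0.36 + 0.0784)] / 0.32² = 0.1422/0.1024 = 1.389, so c = 9.59. Power is 81.6%.

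Both agree with 10 clusters and 80% power. The calculation is therefore on infections per person-year.

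**2. Can the literal definition reach 1.8?**

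- Full follow-up: 375 people over 375 person-years is at most 1.0.
- Person-years planned after losses: 10 × 25 = 250. At 1.8 that is 450 infections, more than the 375 people enrolled. Counting all 375 over 250 person-years gives 1.5.

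So 1.8 is out of reach either way. The low-stratum 0.6 is not.

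**3. What the literal definition would show.** With Poisson infection at the planned rates and a full year, the proportion ever infected is 1 − e^(−λ).

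| Stratum | Control | Intervention | Ratio | Reduction shown | Reduction planned |
|---|---|---|---|---|---|
| High | 1 − e^(−1.8) = 0.835 | 1 − e^(−0.91) = 0.597 | 0.72 | 28% | 49% |
| Low | 1 − e^(−0.6) = 0.451 | 1 − e^(−0.28) = 0.244 | 0.54 | 46% | 53% |

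With gamma variation between HFCAs (CV 0.50 on the rate), the proportions are 0.77 vs 0.56 and 0.43 vs 0.24, with ratios 0.72 and 0.55.

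**4. Power on the person count.** Carrying that rate variation through to the proportions gives CVs of 0.21 and 0.30 (high) and 0.36 and 0.42 (low). The formula then gives 78.6% (high) and 83.6% (low). Simulation with a one-sided t-test on HFCA values gives 78–79% (high) and 84–85% (low). The same simulations on recurrent counts give 85–86% and about 87%.

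**5. Carry-over, as an illustration.** ASSUMPTION: a share q of controls is RDT-negative and PCR-positive at enrolment, each is counted once as new, and none is in MDA. The true ratio is 1.00. On episodes the observed ratio is λ0/(λ0 + q). On persons it is p0/[p0 + q(1 − p0)], because people who would be infected later are counted anyway.

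| q | Low, episodes | Low, persons | High, episodes | High, persons |
|---|---|---|---|---|
| 5% | 0.60/0.65 = 0.92 | 0.451/0.479 = 0.94 | 1.80/1.85 = 0.97 | 0.835/0.843 = 0.99 |
| 10% | 0.60/0.70 = 0.86 | 0.451/0.506 = 0.89 | 1.80/1.90 = 0.95 | 0.835/0.851 = 0.98 |

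**The case against.** The strongest reply is that this is one misplaced noun. The outcome is titled an incidence rate, it is powered on infections, and the model fits recurrent events, so an analyst following the model and the sample size would count infections. That is a fair account of what was probably intended. It does not remove the contradiction: the outcome definition is the place a reader goes to learn what is measured, and it says persons. A rate of 1.8 could also arise if time stopped at the first infection, but the text specifies total person-time over 12 months.

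On *new*, the reply is stronger. A condensed article may leave the operational rule to the full protocol or SAP. The word itself, together with the enrolment PCR sample, already permits excluding infections present at the start. The illustration is also generous. Low-stratum HFCAs lie below roughly 10% prevalence in the peak-season survey, while enrolment falls at the end of the dry season. The RDT figure is an upper value for low-density infections only. DHAp is offered rather than guaranteed, so zero carry-over in MDA is an assumption. These points stand: the absence of a rule here is not in itself an error.

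Nor is it harmless simply to start person-time at the first PCR-negative sample. Carriers cleared by DHAp in MDA would enter the risk set while untreated control carriers might not, so the arms would no longer be compared on like populations.

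**Conclusion.** The definition of a primary outcome contradicts its own sample size and its planned model, and should be corrected. Read literally, it cannot yield the high-stratum baseline. It would show the planned effects as about 28% (high) and 46% (low) instead of 49% and 53%, assuming Poisson infection at the planned rates and full follow-up.

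Three stronger readings are tempting, and the document does not support them:

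- *The trial loses most of its power.* Holding the CV at 0.50 for the person count would give 35–38% in the high stratum. But a proportion with mean 0.835 cannot have a CV above √(0.165/0.835) = 0.44. With the variation carried through properly, power stays close to the stated 80% in the high stratum and above it in the low.
- *The planned rates are impossible in both strata.* Only the high-stratum 1.8 breaches the ceiling.
- *The MDA effect is biased by differential misclassification.* The article nowhere says that persisting infections will be counted as new. The mismatch between PCR outcome and RDT-guided treatment is a risk that differs by arm. Its direction would favour MDA, but its size rests wholly on an assumed q.

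**What to change.** 1. Redefine outcome two as the number of new PCR-detected *P. falciparum* infections, recurrences allowed, divided by person-time at risk. This matches the sample size and the planned Poisson or negative binomial model, neither of which needs to change.
2. Drop the word *cumulative* from the high-stratum sample-size paragraph. Read as a proportion, a cumulative incidence cannot be 1.8.
3. State, or cite from the full plan, one PCR rule for a new infection that is identical in all arms: for example, a PCR-positive visit preceded by a PCR-negative visit. Say what time counts as at risk.
4. Add a sensitivity analysis restricted, in every arm, to people PCR-negative at the enrolment sample. That sample is taken before treatment takes effect, so this starting risk set does not depend on treatment.

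The cost is wording and programming; the enrolment and four-weekly samples already supply the data, and no treatment rule is touched. The downside is some lost person-time, and the sensitivity analysis leaves out people PCR-positive at enrolment.

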MDA and fMDA using DHAp represent two potential strategies to achieve greater clearance of human infection and reduction in the parasite reservoir, and both provide longer chemoprophylactic protection against new infections. The primary aim of this study is to quantify the relative effectiveness of MDA and fMDA with DHAp against no mass treatment for reducing *P. falciparum* parasite prevalence, confirmed out-patient malaria case incidence, and monthly infection incidence in areas stratified by high and low malaria transmission. It is hypothesized that two rounds of fMDA and MDA with DHAp will be significantly more effective than no mass treatment (standard of care) at reducing these health outcomes. A secondary objective of this study is to compare the cost and cost-effectiveness of the fMDA and MDA strategies with DHAp compared to no mass treatment.

Other outcomes related to the quality of program implementation will also be measured during this study to help understand why the MDA and fMDA with DHAp interventions were, or were not, found to be effective in this setting. These outcomes include: participant adherence of taking a full course of DHAp by the fMDA and MDA interventions; clearance of asexual stage parasites at day seven following the administration of DHAp; population coverage of the fMDA and MDA interventions in the study areas; and community acceptability of participating in the fMDA and MDA interventions. Measurement for these outcomes is summarized in the Methods/Design section below, with further details provided in the Additional file 1.

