#### Community-wide mass drug administration with dihydroartemisinin plus piperaquine

Under coordination with the Zambia NMCC, two rounds of MDA with DHAp are being implemented in December 2014 (end of dry season) and February 2015 (beginning of rainy season) in selected study site HFCAs. Spacing of the rounds was determined by the manufacturer recommendation of not receiving more than two courses of DHAp within two months [4]. Each round of the MDA-DHAp intervention consists of testing all individuals with an RDT, sharing the result of the RDT, and then offering an age-appropriate therapeutic dose of DHAp, irrespective of the RDT test result, among those consenting individuals meeting the inclusion criteria to receive DHAp, as outlined below and in Fig. 2. All consenting women in the MDA intervention not in the first trimester of pregnancy are offered DHAp.

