#### Household-level focal mass drug administration with dihydroartemisinin plus piperaquine

Under coordination with the Zambia NMCC, two rounds of fMDA with DHAp are being implemented in December 2014 (end of dry season) and February 2015 (beginning of rainy season) in selected study site HFCAs. Each round of the fMDA-DHAp intervention consists of testing all individuals with an RDT and then sharing the result of the RDT. An age-appropriate therapeutic dose of DHAp is offered to all consenting individuals meeting the inclusion criteria to receive DHAp, as outlined below and in Fig. 3. Among all other consenting eligible individuals in the household where a positive RDT result occurred among any member, an age-appropriate therapeutic dose of DHAp is offered, irrespective of the RDT test result of that individual. All consenting women in the fMDA intervention not in the first trimester of pregnancy are offered DHAp in accordance with the fMDA process just outlined.

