### Rapid diagnostic test positivity during campaign rounds

As described above under the MDA and fMDA intervention descriptions, all individuals aged three-months-old and older in these HFCAs will be tested by RDT for detecting malaria parasite infections; this will then be used for ascertaining primary outcome four (RDT positivity) in each HFCA. RDT positivity in control areas during each of the two rounds of the MDA and fMDA interventions in 2014, and again in 2015, will be obtained through comparing RDT positivity among individuals tested as part of the monthly control cohort during the months when the MDA and fMDA rounds occur.

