### Statistical analysis plan

The primary analysis for estimating the treatment effect between MDA, fMDA, and control HFCAs for primary outcome one (parasite prevalence) and two (parasite infection incidence rates) will be based on intention to treat at the individual level for infections measured by RDT and PCR. The analysis of parasite prevalence will use a logistic or log binomial model, while the analysis for infection incidence will use a Poisson or negative binomial model. Models will include a random intercept at the HFCA level (randomization unit), fixed effect for intervention exposure, time period (pre- and post-intervention), plus other potential confounding factors. Standard errors will be estimated, with the addition of repeated measures among individuals.

Data for total and confirmed OPD and IPD malaria case incidence (outcome three) among all ages will be analyzed on an intention-to-treat basis. Routine data on case counts will be analyzed using a Poisson or negative binomial model, with random intercepts at the HFCA level. The models will include a fixed effect for study arm and time period (pre- and post-intervention), plus other potential confounding factors.

Differences in prevalence measures (RDT positivity) at each round will be assessed using an *X*^2^ test, as well as logistic regression models to account for potential confounding factors, on an intention-to-treat basis. Logistic models will include a random intercept for HFCA, as well as fixed effects for other potential confounding factors. Trends in parasite prevalence across rounds, with the inclusion of the control group, will then allow rapid assessment of the effect of the fMDA and MDA interventions over time, after removing the seasonality effect.

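### Primary outcome four (RDT positivity at each campaign round) is read before that round's drug is given: round one is a baseline, round two can show the effect of one course only, and nothing is read after the second course

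*Protocol article*

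**What the plan says.** The Primary outcome measures section introduces its list as "Primary outcomes used to measures the impact of the MDA-DHAp and fMDA-DHAp interventions, as compared to a control of standard of care". The fourth item is "RDT positivity: defined as the proportion of all individuals tested by RDT at each round of the fMDA and MDA interventions", among people aged three months and older, with a contemporaneous control sample.

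The order of events within a round is set out under Interventions. For MDA, a round means "testing all individuals with an RDT, sharing the result of the RDT, and then offering an age-appropriate therapeutic dose of DHAp". For fMDA, "Each round of the fMDA-DHAp intervention consists of testing all individuals with an RDT and then sharing the result of the RDT", and household treatment then depends on that result. The section on RDT positivity during campaign rounds says of the campaign test that "this will then be used for ascertaining primary outcome four (RDT positivity) in each HFCA". Control values come from the monthly control cohort in the months of the rounds.

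The Study timeline and Trial status sections give two rounds: November to December 2014, and February to mid-March 2015.

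The Statistical analysis plan section states that "Differences in prevalence measures (RDT positivity) at each round will be assessed", by an X² test and by logistic models with a random HFCA intercept. It adds that trends across rounds, with the control group included, will allow a rapid assessment of effect after seasonality is removed. The sample size section claims 80% power for 30% versus 20% (high stratum) and 10% versus 5% (low stratum), control against either intervention arm, without naming a round.

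**The concern.** A measure of impact has to be read after the intervention it measures. This one is read just before, in both rounds. At round one no study drug has been given, so randomised arms can differ only by chance or because the samples differ (the whole campaign population against a control cohort). A formal between-arm test at that point cannot inform on effect. At round two the reading can carry only what the first course did, although the Study design section describes the evaluation as one of two rounds.

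Two misreadings are at stake. A chance difference at round one could be taken for a treatment effect, and a one-course result at round two could be taken for the two-round result. The power statement invites both, because a reader cannot tell which reading it covers.

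**Working it through.** **Timing, from the document's own schedule**

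| Outcome-four reading | Dates | DHAp courses offered before the reading | What an arm contrast can estimate |
|---|---|---|---|
| Round one | Nov–Dec 2014 | 0 | Baseline difference only |
| Round two | Feb–mid-March 2015 | 1 | Effect of the first course |
| After round two | none planned | 2 | No data for this outcome |

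For comparison, outcome one has a survey in April to May 2015, outcome two a cohort followed to November 2015, and outcome three routine data through 2015. All three include time after round two.

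**The plan's power figure**

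Inputs from the sample size section: c = 10 HFCAs per arm; n0 = 375/10 = 37.5 controls per HFCA; n1 = about 5,000 per intervention HFCA; k = 0.31 (high) and 0.41 (low). The 5% one-tailed error is called type two in the text and is read here as type one.

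The Hayes and Moulton formula is:

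power = Φ( √[(c−1)(p0−p1)² / V] − 1.645 ), with V = p0(1−p0)/n0 + p1(1−p1)/n1 + k²(p0² + p1²)

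- High: V = 0.0056 + 0.000032 + 0.0961 × 0.13 = 0.018125. √(9 × 0.01/0.018125) = 2.228. Power = Φ(0.583) = 72.0%.
- Low: V = 0.0024 + 0.0000095 + 0.1681 × 0.0125 = 0.004511. √(9 × 0.0025/0.004511) = 2.233. Power = Φ(0.589) = 72.2%.

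So the stated 80% is not reproduced here. The same formula does reproduce the household-survey figures (80.1% and 80.0%). That shortfall is a separate matter, and the timing point does not rest on it.

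**Power by round**

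At round one p0 = p1 whatever the drug does, so the first term is zero and power = Φ(−1.645) = 5%. At round two, let one course achieve a fraction f of the planned difference. The document gives no f, so it is an assumption shown over a range.

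| f | High stratum | Low stratum |
|---|---|---|
| 1 | 72% | 72% |
| 0.75 | 49% | 50% |
| 0.5 | 28% | 28% |
| 0.25 | 13% | 13% |

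**False positives at round one**

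There are 2 arms × 2 strata = 4 comparisons with no possible effect. At one-sided 5% with valid tests, P(at least one) ≤ 1 − 0.95⁴ = 18.5%. The control group is shared within a stratum, so the two statistics there are positively correlated: 0.62 (high) and 0.71 (low), being the control share of the variance on the inputs above. The chance of at least one is then 8.4% and 8.0% per stratum, or 1 − 0.916 × 0.920 = about 16% overall. These figures assume a test that respects clustering.

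**How noisy the control baseline is**

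The standard error of one control HFCA's round-one value is √(0.3 × 0.7/37.5) = 7.5 points (high) and √(0.1 × 0.9/37.5) = 4.9 points (low). The between-HFCA standard deviations are 0.31 × 30 = 9.3 and 0.41 × 10 = 4.1 points.

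**The case against.** The strongest reply is that the plan already treats round one as a reference. The planned trend across rounds with the control group is a change from round one to round two against control, and calling it a rapid assessment fits an interim signal. This stands in part: it would be wrong to say that the baseline goes unused. But the trend sentence leaves the round-one between-arm test in place, and the trend still ends before the second course.

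A second reply is that the trial's hypothesis is untouched. The Background says "It is hypothesized that two rounds of fMDA and MDA with DHAp will be significantly more effective than no mass treatment", and the outcomes it refers to are parasite prevalence, confirmed outpatient incidence and monthly infection incidence. RDT positivity is not among them. This stands. A reader might infer that the trial cannot test its two-round hypothesis. The document does not support that, since outcomes one to three all include data after round two.

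Third, no passage says that a round-one difference will be reported as efficacy, and the comparison could serve as a balance check. That is fair, and it is why the 18.5% is conditional. The outcome is nonetheless listed as a measure of impact and tested at each round, with no line drawn between the two.

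Fourth, the power text speaks of a decrease, which makes sense only after some treatment and so points to round two. That is the likely meaning, but it should be stated.

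One ambiguity remains. The section on RDT positivity refers to the two rounds in 2014 and again in 2015. If further rounds were meant, a later reading could follow two courses, but every schedule statement gives two rounds in total.

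**Conclusion.** The point holds, confined to outcome four. Its round-one reading is a baseline, its round-two reading can show one course at most, and it has no reading after the second course. Listing positivity at each round as a measure of impact, and testing it at each round, is therefore wrong for round one and mislabelled if round two is presented as the two-round result.

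Size: power at round one is the type one error, 5%. The chance of at least one spurious round-one finding is at most 18.5% (about 16% allowing for the shared control), and this matters only if those tests are read as effects. At round two the power depends on how much one course achieves, which the document does not say.

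A reader might also infer that the outcome is worthless or must lose its primary status. Neither follows. Round two against round one, with controls, can estimate a one-course effect, and changing the status of a primary outcome after registration and after round one is debatable and not needed here. Nor does any passage plan to average the two rounds, so dilution by averaging is not a feature of this plan.

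The conclusion assumes that the test-then-treat order holds at each visit and that there are only two rounds. Households visited late in round one might benefit from neighbours' treatment, but that is not the effect of a completed round.

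**What to change.** 1. In Primary outcome measures and in the Statistical analysis plan section, designate round-one RDT positivity as baseline and drop its between-arm comparison as a test of effect. It may still be tabulated by arm.
2. Define the outcome-four effect as the round-two contrast of each intervention arm with control, taking round one into account. Use either the change from round one against control, which the trend sentence already foreshadows, or adjustment for the HFCA's round-one positivity. Choose one in advance.
3. Label the result the effect of one round, so that evidence on two rounds comes from outcomes one to three.
4. State in the sample size section that the power refers to round two.
5. Clarify the 2014 and 2015 wording so that it agrees with the two-round schedule.

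This is wording only and uses readings already planned. As round one is complete, the change should be dated and made before the arm codes are opened. The real cost is precision. The control baseline rests on about 38 people per HFCA, with a sampling error of 7.5 points in the high stratum and 4.9 in the low stratum. That is close to or above the true spread between HFCAs, so the adjustment will be noisy and may gain little.
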